## Methods and analysis

### Study design

The study is a multi-centre collaborative work conducted by University of Exeter and Ningbo University. Consolidated Standards of Reporting Trials (34) and Template for Intervention Description and Replication (35) checklists will be adopted for guidance and reporting. The *PRO-HIIT* study will employ a two-arm cluster-randomised controlled trial design, with an intervention group and a treat as usual control group. Clusters in this study are eight classes of secondary school students, located in Ningbo City, China. The intervention will be delivered five times per week, commencing at the beginning of the three PE and two PA lessons. The PA lessons serve as a complementary opportunity for students to engage in exercises of their choice on days when PE lessons are not scheduled. Assessments will occur at three time points: baseline (T1), immediate post-intervention (T2) and two-month post-intervention (T3), with T3 aligning with the initial two weeks of a new school term following a two-month unstructured summer holiday. Table 1 presents an overview of the schedule for recruitment, intervention delivery and outcome assessments.

**Table 1 T1:** Overview of the *PRO-HIIT* intervention.

Procedures		Recruitment & pre-intervention measurements				Intervention phase (12 weeks)												Post-intervention measurements			Summer holiday	Follow-up measurements	
	22–26 Jan	26 Feb–22 Mar				25 Mar–14 Jun												17–28 Jun		1–4 Jul	5 Jul–1 Sep	2–13 Sep	
	2023–2024 school term 1	2023–2024 school term 2																				2024–2025 school term 1	
	week 22	week 1	week 2	week 3	week 4	week 5	week 6	week 7	week 8	week 9	week 10	week 11	week 12	week 13	week 14	week 15	week 16	week 17	week 18	week 19		week 1	week 2
Eligibility screening		√																					
Consents & assents																							
Training workshop			√																				
Randomisation					√																		
Maturity				√																			
PA (GENEActiv)					√	√											√	√					
PA (questionnaire)				√														√				√	
Sleep																							
Body composition																							
CRF																							
Muscular strength																							
Bone health																							
Executive function																							
Wellbeing																							
Enjoyment																							
Motivation																							
Affect																							
Self-efficacy																							
Academic assessment	√																			√			
Focus groups																		√			Unstructured days		
Intervention delivery						6-min HIIT 1–2 min: 10 s: 20 s 3–4 min: 15 s: 15 s 5–6 min: 20 s: 10 s			8-min HIIT 1–2 min: 10 s: 20 s 3–6 min: 15 s: 15 s 7–8 min: 20 s: 10 s			10-min HIIT 1–2 min: 10s : 20 s 3–6 min: 15 s: 15 s 7–10 min: 20 s: 10 s			10-min HIIT 1–5 min: 15 s: 15 s 6–10 min: 20 s: 10 s								
HIIT exercises						Jumping Jacks, high knees, burpees, butt kicks, mountain climbers, lunge jumps			Running on the spot, squat jumps, high knees, star jumps, burpees, lunge jumps, mountain climbers, butt kicks			Running on the spot, rocket jumps, high knees, star jumps, burpees, lunge jumps, mountain climbers, butt kicks, jumping jacks, side to side skiers			Students choose exercises from an exercise pool								

HIIT, high-intensity interval training; PA, physical activity; yellow, preparation for the intervention; green, measurements and data collection; red, progressively increased exercise intensity and volume; grey, intervention period.

### Sample size estimation

A sample size estimation was calculated based on CRF using the 20 m shuttle run test (20 m-SRT). Previous studies reported 9 laps of improvement, with effect size of *d* = 0.31 (36) and *d* = 0.69 (37), achieved through 12 or 14 weeks of resistance-based HIIT, respectively. In the current study, a conservative effect size of *d* = 0.31 was utilised for power calculation. Therefore, based on a G*Power (Version 3.1) calculation (38) and using two groups with 80% power at an α of 0.05, it is estimated to recruit 165 participants in each group. With an average enrolment of 50 students in secondary school classes in Ningbo and a conservative 20% of dropout rate (39), it is deemed that 8 classes (approximately 50 participants per class) would provide sufficient statistical power for analysis. Given the typical scale of a Chinese secondary school (10–15 classes per grade), the 8 classes will be recruited from one secondary school.

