#### Statistical analyses

Data entry will be completed by one researcher with a random sample of at least 10% of entries cross-checked by a second researcher for accuracy. Prior to analysis, thorough checks for outliers and errors will be conducted using range and boxplot methods. Additionally, assessments for normality, homogeneity of variances and sphericity will be conducted as needed to verify assumptions. The baseline data for intervention and control groups will be presented and compared at individual level using independent sample *t*-test. An intention-to-treat approach will be adopted to evaluate the effects on outcome variables to avoid bias in exploring the impact of the intervention. Linear mixed-effect models will be used, with random effects, to analyse the impact of groups (intervention and control), timepoints (pre-, post-intervention and follow-up) and group × time interactions. Statistical analyses will be adjusted for the clustering effects at class level. Per protocol sensitivity analysis will be undertaken at the class level. Considering for disruptions such as school holidays, exams, severe weather, a minimum of 30 sessions is considered achievable over the 12-week period. Other sensitivity analyses, such as complete-case analysis, will be conducted where appropriate. Moderators, including sex (male, female), baseline overweight/obese (yes, no) and baseline CRF (healthy vs. needs to improve), will be examined with linear mixed models. Where appropriate, subgroup analyses will be conducted for the significant group-by-moderator interactions. PA, sleep and maturity will be included in the model to eliminate confounding effects. All data analyses will be conducted via IBM SPSS Statistics for Windows (SPSS 28.0; IBM Corporation, Armonk, NY, USA), with an alpha level of 0.05.

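### The 165 per group and 80% power come from an individual-level calculation, so they do not support the claim that eight randomised classes give sufficient power

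*Protocol article*

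**What the plan says.** All references are to the protocol article.

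- **Sample size estimation.** The calculation is based on the 20 m shuttle run, the primary outcome: "a conservative effect size of *d* = 0.31 was utilised for power calculation". The software is G*Power 3.1, and the result is "using two groups with 80% power at an α of 0.05, it is estimated to recruit 165 participants in each group". The section then brings in an average class of 50 and a 20% dropout rate, and concludes that "8 classes (approximately 50 participants per class) would provide sufficient statistical power for analysis". No other adjustment is mentioned.
- **Study design.** The trial has a "two-arm cluster-randomised controlled trial design", with eight classes as the clusters.
- **Recruitment and allocation.** Classes are allocated at random after baseline assessment, stratified by PE teacher.
- **Focus groups.** Four students from each intervention class make up a group of 16, which implies four intervention classes and so four per arm.
- **Statistical analyses.** Linear mixed models cover the three time points with a group-by-time interaction, and "Statistical analyses will be adjusted for the clustering effects at class level".

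**The concern.** The sample size treats students as independent, while the design and the analysis both treat the class as a source of variation. Students in one class share a teacher, a timetable and peer-coaches, so their shuttle-run results may be correlated. Any positive correlation within classes inflates the variance of the difference between arms. With eight classes, that variance is also estimated on few degrees of freedom. The power calculation sets both effects to zero.

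This is the only power justification for the primary outcome. If the 80% is taken at face value, a non-significant result will be given more weight as evidence against the programme than the calculation can bear.

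**Working it through.** **Inputs from the protocol article.** d = 0.31, α = 0.05, power 80%, 165 per group, 8 classes of about 50 and 20% dropout (Sample size estimation); 4 classes per arm (implied under Focus groups).

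**Assumed inputs, because the document gives none.** ICC 0.01, 0.02 and 0.05; baseline (T1–T2) correlation r = 0.7; two-sided testing.

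**Step 1: reproduce the stated figure.** For a two-sided, two-sample t-test with independent observations (noncentral t), power at d = 0.31 is 79.9% with 164 per group and 80.2% with 165. A one-sided test would need only 129. So 165 is exactly the individually randomised, two-sided answer and hides no allowance for clustering.

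**Step 2: is there slack in the enrolled number?** 8 × 50 = 400; 400 × 0.8 = 320; 320 / 2 = 160 per arm, or 40 per class. Even with no clustering, 160 per arm gives 78.9%. Inflating 165 for dropout gives 165 / 0.8 = 206.25, so 207 per arm and 414 in all, against about 400 available. The head count leaves nothing to absorb a design effect. Even if all 200 per arm were retained, the normal approximation holds 80% only up to an ICC of about (200/164 − 1) / 49 = 0.0045.

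**Step 3: add clustering, with no credit for baseline.**
- Design effect: DE = 1 + (40 − 1) × ICC.
- Effective n per arm: 160 / DE.
- Noncentrality: 0.31 × √(effective n / 2).
- Between-class df: 8 − 2 = 6.
- Detectable d at 80% power: (1.960 + 0.842) × √(2 / effective n) by the normal approximation. On 6 df the multiplier 2.802 becomes 3.367.

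| ICC | DE | Effective n per arm | Power, normal / 6 df | Detectable d, normal / 6 df |
|---|---|---|---|---|
| 0.01 | 1.39 | 115.1 | 65% / 51% | 0.37 / 0.44 |
| 0.02 | 1.78 | 89.9 | 55% / 42% | 0.42 / 0.50 |
| 0.05 | 2.95 | 54.2 | 37% / 28% | 0.54 / 0.65 |

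Example at ICC 0.01: 160 / 1.39 = 115.1, and 0.31 × √57.55 = 2.35. Power is then about 65% against the normal critical value of 1.96, and 51% against the 6-df value of 2.447.

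**Step 4: separate the two penalties.** At ICC = 0, moving to 6 df alone takes power from 79% to 64% and the detectable d from 0.31 to 0.38. A good part of the 6-df loss at small ICCs therefore comes from the number of classes and not from the ICC.

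**Step 5: credit the baseline measurement.** Suppose baseline explains the same share of variance at student and class level. The variance is then multiplied by 1 − r² = 1 − 0.49 = 0.51.

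| ICC | Power, normal / 6 df, r = 0.7 |
|---|---|
| 0.01 | 91% / 78% |
| 0.02 | 83% / 68% |
| 0.05 | 62% / 48% |

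**The case against.** The strongest reply is that the power without baseline credit describes an analysis the protocol does not plan. The mixed model includes T1, randomisation follows baseline, and stable class differences largely cancel from a group-by-time contrast. This stands, and it matters. With r = 0.7 and ICC 0.01 the design reaches 91% by the normal approximation, and with an assumed r = 0.8 it reaches 90% even on 6 df. It does not rescue the stated 80%, however: the calculation takes no such credit, and the document gives no correlation that would let a reader take it.

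A reader might therefore infer that the trial cannot reliably detect d = 0.31. The document does not support that. It gives neither the ICC nor the baseline correlation, and it does not say whether d = 0.31 was scaled on raw or change scores.

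Three further points stand in part.
- The protocol fixes no degrees-of-freedom method, and a condensed article need not, so both versions are shown throughout.
- The attrition gap is small: 80.2% against 78.9%. About 52 students per class (207 / 4 = 51.75) would close it, and an intention-to-treat mixed model may keep students with partial follow-up.
- Stratifying by PE teacher may reduce between-class variance, but the gain is not quantified, and strata use up some of the few degrees of freedom.

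Leaving detail to a fuller plan is not an answer here. The article states the method, the number and the conclusion, and the conclusion does not follow from that method.

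**Conclusion.** The point holds as a mismatch of method. The 165 is correct arithmetic for independent students but is applied to a trial of four against four classes, so the statement that eight classes suffice is not supported by the calculation shown. At 160 completers per arm with no baseline credit, every positive ICC puts power below 80%.

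How far below depends on assumptions. Over ICC 0.01 to 0.05, power runs from 65% down to 37% by the normal approximation and from 51% to 28% on 6 df. With r = 0.7 credited at both levels, it runs from 91% to 62% and from 78% to 48%. The true power could lie on either side of 80%, and the protocol gives no basis for saying which. The shortfall of 160 against 165 is a side note.

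**What to change.** Keep the eight classes. In Sample size estimation:

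1. Replace the statement that eight classes are sufficient with the achieved power and the minimum detectable effect for four against four classes of about 40 completers, over a stated ICC range such as 0.01 to 0.05. Use between-class degrees of freedom.
2. If credit is taken for baseline, state the T1–T2 correlation assumed and where it comes from.
3. Say that 165 per group is the requirement under independence, and report the expected yield of about 160 per arm beside it.

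The cost is a recalculation and a few sentences, with no extra participants. The stated power is likely to look less favourable.

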### Recruitment and allocation

An invitation letter will be sent to nearby secondary schools at Ningbo University. When schools express their interest, contacts will be initiated to elucidate the participation requirements. Upon agreement from the schools, invitations will be extended to head teachers and PE teachers of year 7, who will then present the study to students for recruitment. To be eligible for participation, students are required to submit signed assent forms along with signed consent forms from their parents/guardians. Students with health or medical conditions that would restrict their ability to engage in vigorous PA will be excluded from the study. The screening process will involve reviewing the medical examination reports submitted by the participants’ parents or guardians. Classes will be randomly allocated to either *PRO-HIIT* group or control group, via a computer-based random number generator by an independent researcher. The randomisation and allocation will take place after baseline assessment. The randomisation will be stratified by PE teacher, wherein each teacher's classes will be randomly assigned to either the intervention or control group.

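### The sample size section treats the class roll of 50 as 50 participants, and even at full uptake 20% dropout leaves 320 pupils against the required 330

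*Protocol article*

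**What the plan says.** The Sample size estimation section of the protocol article bases the calculation on the 20 m shuttle run. It states that "a conservative effect size of *d* = 0.31 was utilised for power calculation" and, "using two groups with 80% power at an α of 0.05", that "it is estimated to recruit 165 participants in each group".

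It then moves from pupils to classes. The starting figure is a class roll: "With an average enrolment of 50 students in secondary school classes in Ningbo". The one loss it names is "a conservative 20% of dropout rate". From these two figures it concludes that "it is deemed that 8 classes (approximately 50 participants per class) would provide sufficient statistical power for analysis".

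The Recruitment and allocation section sets the conditions for entry. To be eligible, "students are required to submit signed assent forms along with signed consent forms from their parents/guardians". In addition, "Students with health or medical conditions that would restrict their ability to engage in vigorous PA will be excluded from the study", which is judged from medical examination reports supplied by the parents or guardians.

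**The concern.** Two things do not fit together.

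- **Roll and participants.** Within one sentence the average enrolment of a class becomes the number of participants in it. The entry rules admit only pupils who assent, whose parents consent and who pass the medical screen. The roll is therefore the most a class can supply, not what it should be expected to supply.
- **Dropout.** The required number is set against a recruitment figure from which 20% is still to be lost, and the subtraction is not shown. When it is done, the result falls below the requirement.

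What is at stake is how far the stated 80% power can be relied on. A reader would take it that eight classes cover the requirement with dropout allowed for. On the stated inputs there is no margin at all before the first refusal or exclusion is counted.

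**Working it through.** **Inputs.** From Sample size estimation: d = 0.31, alpha 0.05, power 80%, 165 per group, roll of 50, 8 classes, 20% dropout. Sidedness is not stated. Four classes per arm is implied by the Focus groups section, where four pupils from each intervention class make 16. No consent or exclusion rate is given.

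**1. Reproduce the plan's figure.** Normal approximation, two-sided: n = 2(1.960 + 0.842)² / 0.31² ≈ 163.4, so 164 per group. The two-sample t-test gives n = 164.3, so 165, which matches exactly. A one-sided test gives about 130 and does not match. The 165 is therefore the bare two-sided t-test number, with no dropout in it.

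**2. Yield of eight classes at full uptake.**
- Participants: 8 × 50 = 400, or 200 per group.
- After 20% dropout: 400 × 0.80 = 320, or 160 per group.
- Required: 2 × 165 = 330. Shortfall: 330 − 320 = 10.

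**3. Recruitment needed for 330.** 330 / (1 − 0.20) = 412.5, so 413 participants, and 412.5 / 8 = 51.6 per class.

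**4. A possible source of the slip.** Multiplying instead of dividing gives 165 × 1.2 = 198 per group, or 396, which fits within 400. The article does not show its method, so this is a conjecture.

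**5. Power on the plan's own basis** (two-sample t-test, d = 0.31, two-sided alpha 0.05).
- 165 per group: 80.2%.
- 160 per group: 78.9%. The detectable d at 80% power is about 0.31 × √(164.3 / 160) = 0.314.

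**6. Loss the plan can absorb.** 1 − 330/400 = 17.5% for refusal, exclusion and dropout together. The stated dropout alone is 20%.

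**7. Effect of incomplete uptake, illustration only.** Analysable per group = 200 × uptake × 0.80. The uptake values are assumptions.

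| Assumed uptake | Per group | Power at d = 0.31 | Detectable d at 80% power |
|---|---|---|---|
| 95% | 152 | 76.9% | 0.32 |
| 90% | 144 | 74.6% | 0.33 |
| 80% | 128 | 69.5% | 0.35 |

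None of these power figures allows for clustering by class.

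**The case against.** The best reply is that the gap lies within the rounding of the inputs. The class size is given only as approximate, and 51.6 per class is about 3% above 50. The dropout rate is described as conservative, and 17.5% would close the gap. **This stands as to size:** the certain part is 10 pupils and about one point of power. It does not rescue the sentence, because a claim that the number is sufficient has to work at the values the section itself gives.

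Second, a reader might infer that the article promises 165 analysable pupils per group after dropout. **It does not say so.** It speaks of recruiting 165 per group and, separately, of sufficient power. The objection here is that the second statement does not follow from the inputs, not that an explicit promise is broken.

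Third, expected consent is recruitment detail that an article may leave to the full protocol. That would answer a complaint about omission. It does not answer the point that the text puts participants where its own source figure is enrolment. Nor can the 20% be read as covering non-consent: the text calls it dropout, and that reading still gives 320.

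Fourth, the planned analysis is a linear mixed model over three time points, adjusted for class, in which pupils with a missed visit may still contribute. The t-test power is therefore not the trial's power. **This is correct.** The figures are given on the plan's own basis, to test its own statement.

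**Conclusion.** The point holds, at modest size. With eight classes of 50 and 20% dropout, the section's inputs give 320 pupils rather than 330, and 78.9% power rather than 80%, even if every pupil on the roll takes part. This rests on four classes per arm and on the individual-level two-sided t-test that reproduces the plan's 165.

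The more important part is structural: the roll is a ceiling under the entry rules, and the calculation leaves no margin for refusal or medical exclusion. How much power that costs cannot be settled from the article, because it gives no uptake rate.

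Two stronger conclusions may be tempting, and the document supports neither. One is that the trial loses substantial power through this error; beyond the first 10 pupils, every loss shown depends on an assumed uptake. The other is that the entry rules make 165 per group unattainable; they set no numerical cap, and slightly larger classes or slightly lower dropout would reach it if uptake were near complete.

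**What to change.** In Sample size estimation:

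1. Inflate for dropout by 1/(1 − 0.20), which gives 413 participants for 330 analysable.
2. Replace the figure of about 50 participants per class with roll × expected consent and eligibility, and state the rate assumed.
3. In place of the statement that eight classes give sufficient power, report the expected analysable number (about 160 per group at most with a roll of 50) and the matching power or detectable effect.
4. Handle the allowance for clustering by class, a separate point, in the same restatement, so that one individual-level figure is not simply exchanged for another.

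Table 1 places eligibility screening in week 1 of term 2 and randomisation in week 4, and Recruitment and allocation puts randomisation after baseline assessment. The actual eligible and consented count should therefore be known before allocation and can replace the assumed rate.

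The cost is a few rewritten sentences and a slightly less favourable power statement. No extra pupils are needed, and no change to allocation, assessments or analysis.

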### Recruitment and allocation

An invitation letter will be sent to nearby secondary schools at Ningbo University. When schools express their interest, contacts will be initiated to elucidate the participation requirements. Upon agreement from the schools, invitations will be extended to head teachers and PE teachers of year 7, who will then present the study to students for recruitment. To be eligible for participation, students are required to submit signed assent forms along with signed consent forms from their parents/guardians. Students with health or medical conditions that would restrict their ability to engage in vigorous PA will be excluded from the study. The screening process will involve reviewing the medical examination reports submitted by the participants’ parents or guardians. Classes will be randomly allocated to either *PRO-HIIT* group or control group, via a computer-based random number generator by an independent researcher. The randomisation and allocation will take place after baseline assessment. The randomisation will be stratified by PE teacher, wherein each teacher's classes will be randomly assigned to either the intervention or control group.

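### Class allocation is stratified by PE teacher but the stated model has no teacher term, so the test may be conservative if each teacher's classes are split between arms and teachers differ

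*Protocol article*

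**What the plan says.** Study design gives the number of clusters: "Clusters in this study are eight classes of secondary school students". Recruitment and allocation makes the class the unit of allocation and names one stratification factor: "The randomisation will be stratified by PE teacher". The full sentence, whose second half matters below, is: "The randomisation will be stratified by PE teacher, wherein each teacher's classes will be randomly assigned to either the intervention or control group". It does not give the number of PE teachers, the number of classes each has, or whether the arms are balanced within teacher.

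Statistical analyses describes the effect model in three places:
- "Linear mixed-effect models will be used, with random effects, to analyse the impact of groups (intervention and control), timepoints", followed by the group-by-time interaction. The random effects are not listed.
- "Statistical analyses will be adjusted for the clustering effects at class level".
- "PA, sleep and maturity will be included in the model to eliminate confounding effects".

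Sex, baseline overweight and baseline fitness are to be examined as moderators. PE teacher does not appear in that section, either as a fixed or as a random effect.

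**The concern.** PE teacher is the only stratification factor, and there is good reason for it. According to the intervention section and Table 4, PE teachers coordinate and supervise the HIIT sessions, choose the peer-coaches, keep the logbooks and may ease the exercises at their discretion.

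When a stratum is balanced across arms, its effect cancels from the arm difference. If the model then ignores the stratum, its variance stays in the residual between classes, and the reported standard error describes a less precise design than the one used. With eight clusters this class-level error largely decides the result. At an intraclass correlation of 0.05 the between-class variance is 0.05, against a sampling variance of 0.95/40 = 0.024 for a class mean. What is at stake is a test that rejects too rarely and an interval that covers too often, in a trial with little between-class information to spare.

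**Working it through.** **The plan's own figure.** Sample size estimation gives 165 per group for d = 0.31, 80% power and α = 0.05. The normal approximation gives 2 × (1.96 + 0.8416)² / 0.31² = 163.4, hence 164. The two-sided noncentral t gives 165 (power 80.2%). The figure reproduces and does not bear on this point.

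**Inputs from the protocol.** Eight classes; about 50 pupils per class less 20% dropout, so m = 40 analysed per class.

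**Assumed, because the protocol does not give them.** Four classes per arm, with each teacher's classes split equally between arms; two teachers with four classes each, or four teachers with two each; intraclass correlation ρ = 0.05; teacher share of between-class variance q = 30% or 60%. Outcome variance is set to 1. For the group-by-time test, ρ and q must be read as referring to change in fitness, since constant teacher differences in level largely cancel.

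**Formulas for class means.**
- Teacher variance: T = qρ
- Remaining variance: W = (1 − q)ρ + (1 − ρ)/m
- True variance of the arm difference: W(1/4 + 1/4) = W/2
- Expected variance reported without a teacher term: (cT + W)/2. With four teachers c = 1, because the four classes in an arm have four different teachers. With two teachers c = 2/3: each arm holds two pairs, the teacher sum of squares within an arm has expectation 2T, and it is divided by 3.
- Reported SE / true SE = √((cT + W)/W)

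**Numbers.** (1 − 0.05)/40 = 0.02375.
- q = 30%: T = 0.015, W = 0.035 + 0.02375 = 0.05875.
- q = 60%: T = 0.030, W = 0.020 + 0.02375 = 0.04375.

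The ratios below are from the formula. Size, power and half-width are from simulating eight class means and comparing group alone with group plus fixed teacher effects. Power is at the protocol's d = 0.31.

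| Teachers | q | SE ratio, no teacher term | Size, no teacher term | Power, without → with | Mean 95% half-width, without → with |
|---|---|---|---|---|---|
| 2 | 30% | √(0.06875/0.05875) = 1.08 | about 4% | 29% → 31% | 0.43 → 0.42 |
| 2 | 60% | √(0.06375/0.04375) = 1.21 | about 3% | 31% → 40% | 0.41 → 0.36 |
| 4 | 30% | √(0.07375/0.05875) = 1.12 | about 3% | 26% → 25% | 0.45 → 0.50 |
| 4 | 60% | √(0.07375/0.04375) = 1.30 | about 2% | 25% → 31% | 0.45 → 0.43 |

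With a teacher term the SE ratio is 1.00 and the size 5% in every row. At q = 0 the ratio is 1.00 without the term, and adding it costs power: 28% → 26% with two teachers, 27% → 21% with four.

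**Degrees of freedom.** Group only: 8 − 2 = 6, critical t = 2.45. Two fixed teachers: 8 − 3 = 5, t = 2.57. Four: 8 − 5 = 3, t = 3.18. The critical value therefore rises by 3.18/2.45 = 1.30 with four teachers, which cancels most or all of the gain unless teacher differences are large.

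**Wider range.** Over ρ = 0.05 or 0.10 and q = 25–75%, the SE ratio without a teacher term runs from 1.07 to 1.60 and the size from 4.1% down to 1.1%.

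**The case against.** **Silence is not exclusion.** The article does not list its random effects, never rules teacher out, and may leave the full model to an analysis plan that is not shown. A reader might infer that the trial has decided against a teacher term; the text does not support that. What remains is that the article does name its clustering level and its adjusters, and the one stratification factor is absent. Followed as written, the model has no teacher term.

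**The contrast is change, not level.** Allocation follows baseline assessment and the test is group by time, so only teacher differences in change matter. This stands. The protocol gives no figure for such differences, so the table illustrates and does not estimate.

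**The direction depends on the split.** A reader might infer outright that the intervals are too wide. That holds only if each teacher's classes are divided between arms, and the protocol states no balance within teacher; an uneven split would remove the teacher variance only in part. The allocation sentence can also be read as sending all of a teacher's classes to one arm. The error would then reverse: over the same wider range the reported SE would be 0.37–0.90 of the true one and the size 7–40%. The word *stratified* speaks against that reading, so inflated false positives are not a conclusion the document supports. The wording still needs settling.

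**Adjustment may not pay.** A reader might infer that adding teacher always sharpens the result. With four fixed teachers and a 30% share, power falls slightly and the interval widens. This stands as a cost of the remedy. The unadjusted interval in that row is shorter, but its coverage is not the nominal one.

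**Conclusion.** The mismatch is in the text: allocation is stratified by PE teacher and the stated model terms omit teacher. Provided that each teacher's classes are split between arms and that teachers differ in change in fitness, the class-level standard error is too large and the test conservative. At an assumed intraclass correlation of 0.05 and a 30–60% teacher share, the illustrative size is about 2–4% instead of 5%, with a standard error 8–30% too large. If teachers do not differ, nothing is lost.

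Under the split reading the omission does not create false positives, so it does not undermine a positive finding. It is a cheap correction worth making before analysis. Its size rests on an assumed number of teachers, intraclass correlation and teacher share, none of which the protocol gives.

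**What to change.** In Recruitment and allocation, state that each teacher's classes are split between the two arms, and give the number of PE teachers and of classes per teacher. In Statistical analyses, name PE teacher as the stratification factor in all effect models, alongside clustering by class, and specify a small-sample degrees-of-freedom method.

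The cost is one sentence, one model factor and some degrees of freedom. As a fixed effect, teacher uses one between-class degree of freedom with two teachers and three with four. With two teachers the price is small. With four, the interval becomes valid but need not be shorter, and power may fall slightly unless teacher differences are large. A random teacher effect is an option there, but its performance with only four teachers was not tested here and should be checked by simulation before it is adopted. The choice should be fixed before outcome data are seen by arm.
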